## Abstract

**Background:**

Despite the large impact that dietary habits have in the management of diabetes, few tools for supporting healthy eating habits are available for persons with diabetes.

**Objective:**

The aim of this randomized clinical trial is to evaluate the effect of a 12-week, mobile health (mHealth), app-based intervention promoting healthy eating habits among patients with type 2 diabetes.

**Methods:**

The HAPPY (Healthy eating using APP technologY) trial is a randomized clinical trial with two arms aiming to include 200 patients, 18 years of age or older, with type 2 diabetes. Both women and men are eligible for inclusion. Study participants are randomized 1:1 to an intervention group, where they are instructed to use a smartphone app promoting healthy eating, or to a control group, where they receive standard primary care only, for a period of 12 weeks. Each week a new topic (eg, vegetable intake) is introduced via the app. After an introduction text, the user is given a topic-related activity to perform (eg, eat one additional serving of vegetables per day during that week). The app records daily progress and sends automatic reminders or feedback to the user. Dietary intake, body composition, clinical variables, and biomarkers are measured at baseline and at 3- and 6-month follow-ups. An extensive web-based questionnaire comprising several validated questionnaires assessing a number of lifestyle factors is distributed via email at baseline and at 3-, 6-, and 12-month follow-ups; lifestyle factors include, for example, sleep, physical activity, eating behavior, and health-related quality of life. The effect of the intervention on dietary intake (primary outcome) and on glycated hemoglobin and blood lipid levels, body composition, blood pressure, other lifestyle factors, and overall health (secondary outcomes) will be assessed.

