### Aim

We are conducting a randomized clinical trial called the HAPPY (Healthy eating using APP technologY) trial, which is a 12-week mHealth intervention (ie, includes the use of a smartphone app). The main aim of the trial is to evaluate its effect in promoting and improving healthy eating habits (primary outcome) and in improving levels of glycated hemoglobin (HbA_1c_), blood lipids, body composition, and blood pressure, as well as other lifestyle factors and overall health (secondary outcomes) in patients with type 2 diabetes. The aim of this paper is to describe the study design and methodology of the HAPPY trial.

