### Sample Size and Power Calculations

A total of 168 patients (84 per group) will provide 80% power at a 5% significance level to detect a clinically significant change of 4 mmol/mol in HbA_1c_ [18]. A standard deviation of 11.8 mmol/mol was estimated based on the average HbA_1c_ level (mean 53.4 mmol/mol, 95% CI 53.3-53.5) in Stockholm County in 2016 using data from the National Diabetes Register [19]. Based on earlier intervention studies within similar populations, a dropout rate of around 20% is expected. To cover for potential dropout, we will recruit a total of 200 patients (100 per group).

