#### Dietary Intake From the 4-Day Food Record

Dietary intake is measured using a 4-day food record over 4 consecutive days, including at least one weekend day. Participants are given a paper diary and instructed by the study personnel, who are trained nutritionists, to write down everything they eat and drink during the period of recording. Type of meal (ie, breakfast, snack, lunch, dinner, etc) is also recorded. The estimated amount of food and beverages consumed can be recorded in different units, including number of items (eg, number of potatoes), weight (eg, 125 g chicken), or unit of volume (eg, 2 dL of milk or 1 cup of coffee). The participants are requested to maintain their usual diet during the days of recording. The software program Dietist Net (Kost och Näringsdata AB) is used by study nutritionists to calculate nutrient intake from the food records; the nutritionists also check the dietary recordings for completeness when they are returned. In the event of items being recorded in an unspecified way (eg, “fish” or “yogurt” without further specification), information on the most commonly consumed fish or yogurt is obtained from nationwide data [20] and entered into the nutrient calculations. Standard portion sizes available for each food item in the Dietist Net software are used if the amount of food was not specified.

The participants complete the food records, as well as respond to a food frequency questionnaire (FFQ), at baseline and follow-up after 3 and 6 months. While the food records will give detailed information on types of food items, portion sizes, and frequency and timing of intake during the day, data from the FFQs allow for comparison to other studies as well as to follow-up of study participants in this study after 12 months.

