Recruitment of study participants is performed at a number of different primary care centers located in areas with different populations and socioeconomic statuses. This increases the generalizability of our results to different groups of patients. However, the inclusion criteria of being able to communicate in Swedish and having access to a smartphone may be a limitation of the study. Type 2 diabetes is more common with increasing age. This could be a limitation, as knowledge of how to use a smartphone may be limited among older individuals, leading to a younger study population. Nevertheless, over 75% of individuals aged 66-75 years in Sweden use the internet on their phone [7]. While patients with limited knowledge of Swedish are more prevalent in areas of lower socioeconomic status, smartphone usage in Sweden is independent of socioeconomic status, and over 90% of all adults in Sweden own and use a smartphone [7]. The smartphone app was developed for usage on both Android and iOS devices, meaning that most smartphone users can download and use it.

To conclude, the app-based mHealth solution evaluated in the described randomized clinical trial has been developed taking into account the needs of patients, who request mHealth solutions to support a healthy lifestyle, as well as the health care system, which is in need of new, feasible solutions to meet the needs of increasing numbers of patients. Using mHealth strategies, real-time interaction with users is possible and health interventions can be delivered at any time. Further, focusing on diet quality, rather than on specific nutrients, food items, or energy intake, allows the user to apply new knowledge regarding healthy eating habits to his or her current eating patterns, as well as personal and cultural food preferences [41]. Such an individualized approach could be a key factor in promoting and supporting long-term adherence to healthier eating habits among persons with type 2 diabetes.

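### The primary outcome is dietary intake, named only as a domain, while the only power calculation is for HbA1c, a secondary outcome; the primary question has no stated power or detectable difference.

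*Protocol article*

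**What the plan says.** - **Outcome status.** The Abstract (Methods) reads "The effect of the intervention on dietary intake (primary outcome) and on glycated hemoglobin and blood lipid levels" and labels the list from HbA1c onwards as secondary. The Aim section words the primary differently, as an intention to "evaluate its effect in promoting and improving healthy eating habits (primary outcome) and in improving levels of glycated hemoglobin". Its list continues "blood lipids, body composition, and blood pressure, as well as other lifestyle factors and overall health (secondary outcomes) in patients with type 2 diabetes", so HbA1c is again secondary.
- **Sample size.** Sample Size and Power Calculations has one calculation. It sets 84 per group (168 overall) at the 5% level and 80% power "to detect a clinically significant change of 4 mmol/mol in HbA_1c". The SD is 11.8 mmol/mol, expected dropout is about 20%, and the recruitment target is 200 (100 per group). The section does not say that HbA1c is secondary, or why it should stand in for diet.
- **Dietary measurement.** A 4-day food record is kept at baseline, 3 and 6 months, and software is used "to calculate nutrient intake from the food records". The same section says the record also shows food types, portion sizes, and frequency and timing of intake. The Web-Based Questionnaire section adds a 94-item FFQ and six National Food Agency questions.
- **Stated focus.** The Discussion describes the approach as "focusing on diet quality, rather than on specific nutrients, food items, or energy intake".
- **Analysis.** Statistical Analysis applies generalized estimating equations to outcomes in general and singles out no dietary variable.
- **Claimed strength.** The Discussion lists an a priori power calculation among the trial's strengths.

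**The concern.** A reader who sees a primary outcome, a sample size with 80% power and a statement that power was calculated in advance will assume that the first is covered by the second. Here it is not: the calculation concerns a different, secondary variable, and nothing printed shows what the trial can detect in diet.

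The primary outcome is also a domain. A food record yields many nutrients and food groups, and several of them could be put forward as the dietary result. This matters more than usual because participants are not blinded, diet is self-reported, and the Discussion itself accepts that most dietary assessment methods are susceptible to social desirability. If the variable were chosen after results were seen by arm, selective reporting would add to that bias. A null dietary result would be equally hard to read, because no one would know what difference the trial could have found.

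**Working it through.** **1. The power figure as printed (HbA1c).** Inputs from Sample Size and Power Calculations: difference 4, SD 11.8, significance level 5%, power 80%, 1:1 allocation. Sidedness is not stated; two-sided is assumed.

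- n per group = 2 × [(1.960 + 0.842) × 11.8 / 4]² = 136.6, so 137 per group (274 in total). The stated 84 per group is not reproduced.
- Power at 84 per group: 4 / (11.8 × √(2/84)) = 2.197; Φ(2.197 − 1.960) = 59%. A one-sided test gives 71%.
- Power at 80 per group: 57%.
- The stated 84 would follow with an SD of about 9.25, a difference of about 5.1, or a baseline-to-follow-up correlation of about 0.62 under baseline adjustment. The article states none of these.

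So the calculation concerns the secondary outcome, and it does not give 80% for that outcome from its own inputs.

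**2. Power for the dietary primary.** The article gives no dietary variable, target difference or SD, so no sample size can be computed. Only a standardised detectable difference is available, for one pre-named variable at two-sided 5% and 80% power: d = (1.960 + 0.842) × √(2/n).

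| n per group | Source | Detectable difference |
|---|---|---|
| 80 | 100 less 20% dropout | 0.443 SD (0.446 with the t distribution) |
| 84 | stated analysis size | 0.432 SD |
| 100 | no dropout | 0.396 SD |

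Power at 84 per group over an assumed range of true effects is 25% for 0.2 SD, 49% for 0.3 SD, 74% for 0.4 SD and 90% for 0.5 SD. Baseline adjustment would help: with an assumed correlation of 0.5, 0.443 × √(1 − 0.25) = 0.38 SD at 80 per group.

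**3. What is left open.** Setting the sections side by side narrows the choice:

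- *Time point:* the Hypothesis section points to 12 weeks, with maintenance after a further 12.
- *Instrument:* the Discussion gives the food record the job of assessing dietary intake, and gives the FFQ long-term follow-up and comparison with other studies.
- *Variable:* no section names one.

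**4. Error rate if several dietary variables were tested.** The article gives no number of tests, so k is assumed, each test at 5%. For independent variables the chance of at least one false positive is 1 − 0.95^k.

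| k (assumed) | Independent | Equal correlation 0.5 (assumed) |
|---|---|---|
| 5 | 23% | 18% |
| 10 | 40% | 29% |

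Variables from one food record are correlated, so the independent column is an upper-end illustration.

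**The case against.** The strongest reply is that this is a journal article. A full protocol or analysis plan may name one dietary variable, define its scoring and set a multiplicity rule, and an article may leave those to it. That stands as far as score construction and multiplicity rules go; their absence here is not a fault. It does not remove the mismatch between the primary outcome and the powered outcome, because both halves are printed.

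Three stronger readings are tempting, and the article does not support them.

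- *The record and the FFQ are interchangeable routes to a primary result.* The article gives them different roles. It does not formally designate the record as the primary instrument, but it plainly leads.
- *No dietary measure matches the stated target of diet quality.* The statement about diet quality describes the app's approach and does not define an outcome. A quality score can be built from the record, and the six National Food Agency questions address overall dietary habits.
- *Every dietary variable will be tested at 5% as primary.* The 5% level appears only in the HbA1c calculation, and Statistical Analysis does not announce a set of primary dietary tests. The error rates above are therefore conditional and do not describe a stated plan.

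It could also be argued that HbA1c is a sensible sizing variable because it is objective and clinically interpretable. That would be a legitimate choice if stated and justified, but the article does neither.

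**Conclusion.** The point holds in this form. The article makes diet primary and HbA1c secondary, calculates power only for HbA1c, and names no single dietary variable, so the primary question has no stated power or detectable difference. This follows from the printed text whatever an analysis plan may contain. That the choice of variable is open is established for this article only, and a fuller document could close it.

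With 80 per arm, one pre-named dietary variable could be detected at about 0.44 to 0.45 SD (two-sided 5%, 80% power, no baseline adjustment). Whether that is adequate cannot be judged without a target difference. The rise in false positives, to about 23% for five or 40% for ten independent tests, rests on assumed numbers of tests and is lower under correlation. The HbA1c figure itself corresponds to about 59% power at 84 per group, assuming a two-sided comparison without baseline adjustment.

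**What to change.** Before any outcome is compared by arm:

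1. Designate one pre-specified variable from the 4-day food record at 3 months as primary, compared between arms with adjustment for its baseline value. One named diet-quality score would suit the stated focus on overall diet. A single pre-named food or nutrient would also answer the objection. If a score is used, name it and fix its scoring, or the choice merely moves to the score.
2. Label other nutrients, food groups and FFQ results as secondary.
3. State that the power paragraph concerns the secondary outcome HbA1c, and correct it: about 59% at 84 per group on the printed inputs, or state and justify the baseline correlation that would give 80%. Relabelling alone would keep a figure that does not follow from its inputs.
4. Add the detectable difference for the dietary primary, about 0.44 to 0.45 SD at 80 per arm, and align the Discussion's claim about power with it.

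The cost is an amendment, analysis-plan wording and, for a score, programming it from data already being collected. No new visits or participants are needed. The downside is that individual nutrients lose any claim to primary status.

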**Results:**

Data collection is ongoing. Recruitment of participants started in January 2019. Findings from the study are expected to be published by the end of 2021.

**Conclusions:**

Technology development provides new ways to promote and support long-term adherence to healthier eating habits. mHealth-based approaches allow for real-time interaction and the delivery of an intervention at any time. Further, focusing on overall diet allows the user to apply new knowledge to current eating patterns, creating an individualized approach. In this study, we evaluate the effect of using a new smartphone app promoting healthy eating habits on dietary intake, clinical markers, and lifestyle factors among patients with type 2 diabetes.

**Trial Registration:**

ClinicalTrials.gov NCT03784612; https://clinicaltrials.gov/ct2/show/NCT03784612

**International Registered Report Identifier (IRRID):**

DERR1-10.2196/24422

## Introduction

### Background

The prevalence of type 2 diabetes is increasing in Sweden, as well as in the rest of the world. Today, over 400 million adults have diabetes [1]. It has long been known that persons with type 2 diabetes have an increased risk of cardiovascular disease (CVD) and premature death, in large part due to an increased prevalence of risk factors for CVD (eg, obesity, dyslipidemia, and hypertension) [2].

More than 80% of patients with type 2 diabetes in Sweden are overweight or obese [3]; excess adiposity, in particular visceral obesity, as well as insulin resistance are strongly associated with an increased risk of both type 2 diabetes and CVD [4]. A healthy diet is the key factor in both prevention and management of type 2 diabetes. Patterns of vegan, vegetarian, and Mediterranean diets have been shown to improve glycemic control in patients with type 2 diabetes in randomized clinical trials [5]. An unhealthy lifestyle (eg, with poor dietary habits and physical inactivity), on the other hand, increases the risk of developing the disease, as well as the risk of complications [1]. In addition to CVD, complications can be serious and may include kidney failure, blindness, and amputation of lower extremities, and could lead to premature death.

Despite the large impact of dietary habits in the management of type 2 diabetes, few tools for supporting dietary changes and maintenance of a healthy diet are available. One strategy to improve health is regular visits to health clinics [6]. This may not always be a feasible strategy given the large number of patients in need of support. To meet both the needs of the patients and the capacity of the health care system, new strategies must be developed. Mobile health (mHealth) (ie, the use of mobile devices, including smartphones, to promote health) is one way to bridge the gap between what patients need and what health care can offer.

In Sweden, over 90% of adults own and use a smartphone [7], making an app-based intervention feasible for implementation in the general population of patients with type 2 diabetes. Technology-driven diabetes prevention programs (ie, utilizing, for example, text messages, email, automated phone calls, websites, etc) focusing on diet and/or physical activity have been evaluated in several intervention studies focusing on weight loss with promising results [8]. Michaelides et al [9] also showed that a fully mobile diabetes prevention program including a dietary component could facilitate weight loss and weight maintenance. Further, results from two recent reviews summarizing smartphone apps targeting diet have also shown promising results with regard to dietary intake in particular, although none of the apps had been developed for, or evaluated in, patients with type 2 diabetes specifically [10,11]. Nevertheless, among patients with type 2 diabetes, an automated web-based program to support healthy diet has been shown to improve dietary habits when assessed using a quality dietary score [12], and improvements in adherence to the Mediterranean diet and in diet quality overall have been shown after the use of a smartphone app during a period of 3 months [13]. Thus, mHealth strategies show potential as a tool to promote and support healthy eating habits, including among type 2 diabetes patients.

### Aim

We are conducting a randomized clinical trial called the HAPPY (Healthy eating using APP technologY) trial, which is a 12-week mHealth intervention (ie, includes the use of a smartphone app). The main aim of the trial is to evaluate its effect in promoting and improving healthy eating habits (primary outcome) and in improving levels of glycated hemoglobin (HbA_1c_), blood lipids, body composition, and blood pressure, as well as other lifestyle factors and overall health (secondary outcomes) in patients with type 2 diabetes. The aim of this paper is to describe the study design and methodology of the HAPPY trial.

### Hypothesis

Our hypothesis is that participants randomized into the intervention group, who will use the smartphone app, will have improved their dietary habits, cardiovascular risk factors, and other lifestyle factors after 12 weeks of active intervention compared to the control group, who will receive standard care. Further, we hypothesize that improved habits will be maintained after an additional 12 weeks of follow-up.

## Methods

### Study Design

The HAPPY trial is a randomized clinical trial with two arms. The research team behind the design of the smartphone app and the study includes nutritionists, epidemiologists, statisticians, and clinicians. The intervention is described according to the CONSORT (Consolidated Standards of Reporting Trials) statement [14] and the CONSORT-EHEALTH (Electronic and Mobile HEalth Applications and onLine TeleHealth) checklist developed specifically for eHealth and mHealth interventions [15].

Patients with type 2 diabetes who volunteer to participate are recruited from primary health care centers in the center and suburbs of Stockholm. Data collection is performed in collaboration with clinicians and nurses at the centers, where they give a brief introduction of the study to their patients. Information about the study is also available in the waiting rooms of the centers, and patients can contact study personnel directly if they are interested in participating. The included primary care centers differ in size, and the number of eligible patients can vary. Those interested in participating in the study are contacted by phone by study personnel and are given more information. Patients that fulfill inclusion criteria and agree to participate are sent an email with a link to the baseline questionnaire, including a web-based consent form. They are thereafter scheduled for a meeting with study personnel. During this meeting, participants sign an additional written informed consent form in order to verify that they fully understand the web-based information. Thereafter, baseline measurements are performed and patients are then randomized 1:1 to the intervention or control group. All participants are followed up after 3, 6, and 12 months.

Baseline and follow-up assessments at 3 and 6 months include an extensive web-based questionnaire including assessment of lifestyle factors; a 4-day food record; clinical measurements of height, weight, waist circumference, blood pressure, and body composition; and blood sampling for measurement of HbA_1c_ and serum lipids. After 12 months, participants are followed up with a final web-based questionnaire. All participants continue to receive usual care by their primary caregiver (ie, they visit their primary caregiver as planned as if they had not been part of the study). Participants randomized to the intervention group use the smartphone app during the 12 weeks of the active intervention from baseline, while participants in the control group will use the app during the 12 weeks after the first follow-up at 3 months. Participants are encouraged to use the app daily, but there is no requirement of how often participants should use the app. The study design is presented in Figure 1.

